
### Sample size estimates

With 54 pharmacists per group, the study will have an 80% power to detect an effect size of 0.60 between the study groups for two primary outcomes which are numeric (knowledge and skills scales) using the independent *t* test with a significance level of 0.025%. In addition, with 54 pharmacists per group, the study will be able to detect a difference of at least 27.5% between the two study groups for any dichotomous outcome using the chi-square test with 80% power and a significance level of 5%. Assuming a loss-to-follow-up rate of 10%, the study will randomize 60 pharmacists per group for a total of 120 pharmacists. With over 1000 community pharmacists practicing in Qatar, including 60 pharmacists in each group is achievable. We will select a random sample of 200 pharmacists for recruitment as we anticipate that some pharmacists will not accept to participate. Once the sample size of 120 is reached the recruitment will stop.

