
To be competent in providing tobacco-cessation interventions and to offer effective tobacco-cessation programs, pharmacists should have the necessary competence, skills, and confidence in relation to tobacco cessation. Several educational interventions were designed and implemented to enhance the knowledge and skills of healthcare professionals in relation to tobacco cessation [27]. Yet the majority of these interventions were implemented and assessed outside the Middle East (ME) region and did not target pharmacists. In addition, these interventions were only delivered by one group of professionals (e.g., nurses, physicians, or pharmacists) with expertise in smoking cessation programs. In an effort to build the capacity of pharmacists on tobacco-use treatment, the aim of this study is to design, implement, and evaluate an intensive education program on tobacco treatment for pharmacists in Qatar. We hypothesize that pharmacists who participate in the program will have better knowledge, attitudes, perceived self-efficacy and skills in relation to tobacco-use treatment than pharmacists who receive no such program (control group).

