### Outcome measures

The study has two primary outcomes: post-intervention tobacco-related knowledge and post-intervention skills for tobacco cessation assessed using a multiple-choice-based evaluation instrument and an OSCE, respectively. The secondary study outcomes are post-intervention attitudes towards tobacco cessation and self-efficacy in tobacco-cessation interventions assessed using a survey instrument. An additional secondary study outcome is the post-intervention performance difference in relation to tobacco-cessation skills in the practice setting assessed using the simulated client approach.

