### Statistical analysis

Data will be analyzed using IBM SPSS (IBM SPSS® for Windows, Version 24.0; IBM Corp, Armonk, NY, USA). The Consolidated Standards of Reporting Trials (CONSORT) guidelines will be followed when analyzing the study data [34]. Demographic and other pharmacist education and practice-related questions, along with baseline knowledge, attitudes, and perceived self-efficacy, will be summarized using means and standard deviations for numeric variables such as age and year of experience and frequency distribution for categorical variables such as gender, country of education, etc. Those will be compared between the study groups so that differences will be used to adjust the primary analyses.

The primary analyses will include comparing post-knowledge scores between the two study arms using the independent *t* test and the skills-related scores on the OSCE using the same method. The secondary analyses will include adjusting the main analyses to any imbalances in baseline variables that are observed between the study arms. This will be done using the linear regression method. Moreover, knowledge scores will be compared within each study group using the paired *t* test. For outcomes that are dichotomous or that will be dichotomized, such as the percentage of pharmacists with a specific attitude or self-perceived efficacy, then the chi-squared test will be used to compare such outcomes between study groups and the McNemar test will be used to compare responses within each study group over time. Performance on the simulated patient will be compared in a similar manner as the outcomes above depending on whether it is dichotomized or not. In addition, repeated-measures analysis (depending on the scale of measurement for each outcome) may be used to detect whether there is an intervention × time interaction so that difference between study groups is changing over time or not. The level of statistical significance will be set at 5%.

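### The two primary outcomes are powered at a split significance level but analysed at an unsplit 5%; a Holm rule would reconcile the two sections and gain power at little cost

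*Protocol article*

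**What the plan says.** All statements are in the protocol article.

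- Outcome measures: "The study has two primary outcomes: post-intervention tobacco-related knowledge and post-intervention skills for tobacco cessation". Knowledge is measured by a multiple-choice instrument and skills by an OSCE.
- Sample size estimates: counting 54 evaluable participants in each arm, "the study will have an 80% power to detect an effect size of 0.60 between the study groups for two primary outcomes". Both outcomes are numeric scores compared by t test, and the level is given as "with a significance level of 0.025" (printed with a percent sign). The same section uses 5% for any dichotomous outcome.
- Statistical analysis: "The primary analyses will include comparing post-knowledge scores between the two study arms", and OSCE scores are compared by the same test. The section ends: "The level of statistical significance will be set at 5" per cent. It mentions no division of that level between the two primary tests.
- Background: the hypothesis is that trained pharmacists "will have better knowledge, attitudes, perceived self-efficacy and skills in relation to tobacco-use treatment than pharmacists who receive no such program".

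No section states whether one primary outcome is enough for success or both are needed.

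**The concern.** The two sections that fix the significance level for the primary outcomes disagree. The sample size was worked out at a level that only makes sense as half of 5%, printed with a stray percent sign. The analysis section names 5% and carries no split. An analyst who follows the analysis section literally runs two primary tests at 5% each and loses the error control that the sample size paid for. An analyst who follows the sample size section uses a fixed 2.5% for each, which is valid but gives away power that a step-down rule would keep.

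The 80% also carries no label saying that it is per outcome. At stake are the false-positive rate of the trial's primary claims, and some power that can be recovered without recruiting anyone.

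**Working it through.** **Inputs.** From Sample size estimates: 54 evaluable per group, standardised effect 0.60 for both outcomes, equal groups, independent t test. Assumed: two-sided tests (sidedness is not stated) and a within-group correlation between the two scores of 0 to 0.7 (not in the protocol).

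**1. Reproduce the 80%.** The noncentrality is 0.60 × √(54/2) = 3.118 on 106 degrees of freedom. Exact noncentral t power for one outcome:

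| Level | Two-sided | One-sided |
|---|---|---|
| 2.5% | 79.9% | 87.1% |
| 5% | 87.1% | 92.7% |
| 0.025% as printed | 26.0% | 32.6% |

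Of these readings, only two-sided 2.5% gives the stated 80%. The normal approximation at that level gives 81.0%. So the percent sign is a slip, and the planning level is 5%/2.

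**2. Family-wise error if 5% is applied to each primary test.** For independent tests, 1 − 0.95² = 9.75%; positive correlation makes it smaller. At 2.5% each it is 1 − 0.975² = 4.94%.

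**3. Fixed split against Holm, both true effects 0.60.** Holm tests the smaller p-value against 2.5% and, if that is met, the other against 5%. At correlation 0 the results follow directly from step 1:

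- Both significant, fixed split: 0.799² = 0.639.
- Both significant, Holm: 0.8706² − (0.8706 − 0.7993)² = 0.758 − 0.005 = 0.753.
- Per outcome, Holm: 0.7993 + (0.8706 − 0.7993) × 0.7993 = 0.856.

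For other correlations, trials were simulated (200,000 per row, simulation error about 0.1 percentage point):

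| Assumed correlation | Both, fixed 2.5% | Both, Holm | Per outcome, Holm | At least one (either rule) |
|---|---|---|---|---|
| 0 | 64.0% | 75.3% | 85.7% | 96.0% |
| 0.3 | 66.4% | 76.7% | 85.0% | 93.3% |
| 0.5 | 68.6% | 78.1% | 84.8% | 91.4% |
| 0.7 | 71.2% | 79.7% | 84.3% | 88.8% |

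Per-outcome power under the fixed split is 80% throughout. Holm's gain for both outcomes runs from 75.3 − 64.0 = 11.3 points down to 79.7 − 71.2 = 8.5 points. With no true effect on either outcome, the chance of any rejection is the same under Holm as under the fixed split, at most 5%.

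**The case against.** A reader might infer that the plan promises 80% power to show both outcomes and so falls short, at 64–71%. The protocol does not support that reading. The sample size sentence describes an ordinary one-outcome t-test calculation, and it is correct as such. Splitting 5% in two suits a design in which either outcome may support a claim; if both had to succeed, no split would be needed. The hypothesis in the Background cannot serve as a both-must-succeed rule, because it also lists attitudes and self-efficacy, which Outcome measures makes secondary. This part of the objection stands, and the 64–71% is used here only to compare testing rules.

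It can also be said that a fixed Bonferroni split is valid, so preferring Holm is a matter of efficiency. That stands too. Holm is offered as an improvement, and it has a price: the fixed split comes with simple matching 97.5% confidence intervals, and Holm does not. If the team did intend to require both outcomes, testing each at 5% would be valid and would give slightly more joint power than Holm (76–81%).

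Finally, the 5% may be meant as a general default, or as the family-wise level, with the multiplicity rule left to a statistical analysis plan that is not shown. That is possible. But the protocol itself states two levels for the same two tests and does not connect them, so the mismatch is in what is written and not in what is omitted.

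**Conclusion.** The point holds as an inconsistency between two sections, together with a cheap improvement. The sample size rests on two-sided 2.5% per primary outcome (misprinted as 0.025%), while the analysis section gives 5% without a split. Taken literally for both primaries, the latter allows a family-wise error of up to about 9.7% when the tests are independent.

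The 80% needs a label, not a correction. Holm uses both printed levels coherently. Its size of benefit over a fixed split is 4 to 6 points of power per outcome and about 8 to 11 points for both together. These gains rest on two-sided tests, true effects of 0.60 on both outcomes, 54 evaluable per group, and an assumed correlation of 0 to 0.7.

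**What to change.** In Statistical analysis, state that the two primary outcomes are tested by Holm at a family-wise two-sided 5%: the smaller p-value against 2.5% and, if that is met, the other against 5%. Say that the 5% level otherwise applies to the remaining analyses.

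In Sample size estimates, correct the printed level to 2.5% two-sided and label the 80% as the minimum power for each primary outcome separately at effect size 0.60. If a figure for both outcomes is given, print the assumed correlation beside it.

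The cost is two or three sentences, with no extra participants and no added family-wise error. The team loses the simple 97.5% intervals that match a fixed split, and should say in advance which intervals it will report. Trial status describes recruitment as still to come, so on that timing the rule could be fixed before any outcome data existed.

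### The significance level for the two primary outcomes is printed as 0.025%, 100 times too small for the stated sample size and power

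*Protocol article*

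**What the plan says.** The outcome section of the protocol article names two primary outcomes, knowledge and skills: "The study has two primary outcomes: post-intervention tobacco-related knowledge and post-intervention skills for tobacco cessation".

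The section on sample size estimates gives one power statement for both: "With 54 pharmacists per group, the study will have an 80% power to detect an effect size of 0.60", and the test is specified as an independent t test "with a significance level of 0.025", with a percent sign directly after the figure. The next sentence of that section treats dichotomous outcomes, with 80% power at a significance level of 5%. Allowing for 10% loss to follow-up, 60 per group and 120 in total are to be randomized.

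The statistical analysis section names the primary analyses as "comparing post-knowledge scores between the two study arms using the independent *t* test", and the same test for the OSCE skills scores. It closes with a general sentence: "The level of statistical significance will be set at 5", again followed by a percent sign. It mentions neither 0.025% nor 2.5%, nor any division of the level between the two primary outcomes.

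**The concern.** A level of 0.025% is 0.00025. That is an unusual threshold for a trial of this kind, and 54 per group looks far too few for it at an effect size of 0.60. The neighbouring 5% shows that the percent sign is used in its ordinary sense in that section, so the figure cannot be excused as house notation.

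The sample size statement is the only trace of a separate significance level for the two primary outcomes. If it is misprinted, the article shows two thresholds, 0.025% and 5%, and neither produced the sample size. A primary comparison with p = 0.03 would succeed at 5% and fail at 2.5% and at 0.025%. One with p = 0.01 would succeed at 5% and 2.5% and fail at 0.025%. The rule should be clear in writing before data are seen, because with two primary outcomes the choice between 5% and 2.5% for each also decides whether the overall false-positive rate is held at 5%.

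**Working it through.** **Inputs, all from the sample size section:** n = 54 per group, equal groups; standardized effect d = 0.60; independent t test; stated power 80%; printed level 0.025% = 0.00025; 10% loss to follow-up. Whether the test is one- or two-sided is not stated. Two-sided is assumed, and one-sided is shown for comparison.

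**Formula.** The degrees of freedom are 2n − 2 = 106. The noncentrality is d × √(n/2) = 0.60 × √27 = 3.118. Two-sided power is the probability that a noncentral t variable with these parameters falls beyond ± the critical value t(1 − α/2; 106).

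**Can the plan's 80% be reproduced?**

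| Level α | Critical value (two-sided) | Power, 54 per group, two-sided | Power, one-sided | n per group for 80%, two-sided |
|---|---|---|---|---|
| 0.00025 (0.025%, as printed) | 3.791 | 26.0% | 32.6% | 117 |
| 0.025 (2.5%) | 2.274 | 79.9% | 87.1% | 55 |
| 0.05 (5%) | 1.983 | 87.1% | 92.7% | 45 |

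- At the printed level no variant comes near 80%. The normal approximation gives 29.3% two-sided and 35.8% one-sided. If all 60 randomized per group were analysed, two-sided power would still be only 32.0%.
- At 2.5% two-sided the plan's figure is reproduced: 79.9% with the t distribution and 81.0% with the normal approximation. The n for 80% is 55 and 53 respectively, either side of the printed 54.
- At 5% two-sided, 45 per group would suffice, so 54 does not come from an undivided 5%.

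**Backwards from the plan's figures.** Solving for the two-sided level at which n = 54 and d = 0.60 give exactly 80% power yields α = 0.0252.

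**Detectable effect at 80% power with 54 per group, two-sided:** 0.600 at α = 0.025, and 0.895 at α = 0.00025.

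**Loss to follow-up.** 54 / (1 − 0.10) = 60 per group, and 2 × 60 = 120. This agrees with the plan and does not depend on the printed level.

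**Link to two primary outcomes.** 5% / 2 = 2.5%, the level that reproduces the plan. The article does not state this reasoning.

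**The case against.** The strongest reply is that this is a stray percent sign. The author meant 0.025, the calculation was run at 0.025, and 54, 60 and 120 are right. On that view, 26% power, 117 per group and a detectable effect of 0.90 describe a trial that nobody planned. That is correct: those numbers prove that the printed level is wrong. They do not measure lost power.

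A second reply is that the analysis section does give a level, 5%, and that 2.5% for each of two outcomes is compatible with an overall 5%. The compatibility is real once the slip is corrected, but the article does not say whether its 5% is an overall level or applies to each test. A reader cannot recover 2.5% from the text without redoing the power calculation. Whether the 5% is to be divided is a separate question from the misprint, and correcting the sample size section alone would not settle it.

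Two cautions about the remedy also stand. The article states neither two-sidedness nor division of 5% by two. A one-sided test at 0.0125 has the same 79.9% power, so the sponsor should confirm what was intended. And 2.5% must not simply replace the 5% in the analysis section, because that sentence also covers the other analyses, and the sample size section powers dichotomous outcomes at 5%.

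**Conclusion.** The concern holds. The printed 0.025% is 100 times smaller than the level behind the sample size. With 54 per group and d = 0.60, power is 26.0% at the printed level (32.6% if one-sided) and 79.9% at 2.5% two-sided.

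The error is in the stated threshold and not in the size of the trial. It still needs correcting, because a significance level for the primary outcomes governs how the trial is read, and the only other level in the article, 5%, does not match the calculation either. The 2.5% reading assumes a two-sided test; the finding that 0.025% is wrong does not depend on that assumption.

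**What to change.** - **Sample size section:** replace 0.025% with a two-sided significance level of 2.5% (0.025) for each of the two primary outcomes, being 5% divided by two. The sponsor should confirm that the test was planned as two-sided and that the division between the two outcomes was intended.
- **Statistical analysis section:** state the same 2.5% for the knowledge and OSCE skills comparisons, and make clear that 5% applies to the other analyses.

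The cost is one corrected figure and one aligned sentence. Sample size, recruitment and conduct do not change. The correction should be made before outcome data are seen.

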### Statistical analysis

Data will be analyzed using IBM SPSS (IBM SPSS® for Windows, Version 24.0; IBM Corp, Armonk, NY, USA). The Consolidated Standards of Reporting Trials (CONSORT) guidelines will be followed when analyzing the study data [34]. Demographic and other pharmacist education and practice-related questions, along with baseline knowledge, attitudes, and perceived self-efficacy, will be summarized using means and standard deviations for numeric variables such as age and year of experience and frequency distribution for categorical variables such as gender, country of education, etc. Those will be compared between the study groups so that differences will be used to adjust the primary analyses.

The primary analyses will include comparing post-knowledge scores between the two study arms using the independent *t* test and the skills-related scores on the OSCE using the same method. The secondary analyses will include adjusting the main analyses to any imbalances in baseline variables that are observed between the study arms. This will be done using the linear regression method. Moreover, knowledge scores will be compared within each study group using the paired *t* test. For outcomes that are dichotomous or that will be dichotomized, such as the percentage of pharmacists with a specific attitude or self-perceived efficacy, then the chi-squared test will be used to compare such outcomes between study groups and the McNemar test will be used to compare responses within each study group over time. Performance on the simulated patient will be compared in a similar manner as the outcomes above depending on whether it is dichotomized or not. In addition, repeated-measures analysis (depending on the scale of measurement for each outcome) may be used to detect whether there is an intervention × time interaction so that difference between study groups is changing over time or not. The level of statistical significance will be set at 5%.

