#### Assessment implementation

The assessment instruments will be distributed to participants in both groups prior to, and following, the program. The assessment will be likely online using a survey software. Participants will be allowed a certain predetermined time to complete the evaluations. Unique participants’ codes will be created to link the pre to post data for the same participant.

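### The primary knowledge test leaves out the linked pre-program score, covariates enter only after an imbalance is seen, and the article gives that adjustment two different roles

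*Protocol article*

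**What the plan says.** Under Assessment implementation, the knowledge instrument is given at both times in both arms: "The assessment instruments will be distributed to participants in both groups prior to, and following, the program". The scores can be paired: "Unique participants’ codes will be created to link the pre to post data for the same participant".

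The Statistical analysis section does not use that pairing in its main comparison. For knowledge, "The primary analyses will include comparing post-knowledge scores between the two study arms using the independent" t test. The other primary outcome is handled likewise: "and the skills-related scores on the OSCE using the same method".

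The same section describes covariate adjustment twice. Its first paragraph lists demographic and practice variables together with baseline knowledge, attitudes and self-efficacy, and says: "Those will be compared between the study groups so that differences will be used to adjust the primary analyses". Its second paragraph says: "The secondary analyses will include adjusting the main analyses to any imbalances in baseline variables that are observed between the study arms", by linear regression. Neither paragraph defines an imbalance.

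Pre-program knowledge otherwise appears in within-arm paired t tests and in a repeated-measures analysis that is optional.

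The sample size rests on the unadjusted test: "With 54 pharmacists per group, the study will have an 80% power to detect an effect size of 0.60 between the study groups".

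**The concern.** There are three linked difficulties.

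1. **Precision.** A pre-program score on the same instrument is a natural covariate for the post-program score. A test that omits it has a larger residual variance than it needs whenever the two scores are correlated.

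2. **Covariate selection.** Allocation is by concealed permuted blocks, so baseline differences between arms are due to chance. Their size does not show which variables predict the outcome. Selecting covariates on observed differences makes the model depend on the data and usually leaves a useful covariate out.

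3. **Status of the result.** If the adjustment belongs to the primary analyses, chance imbalance selects the primary model. If it is secondary, the t test is fixed and imbalance selects only a supporting model. When the two analyses disagree, the article does not settle which one is confirmatory.

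**Working it through.** **Inputs.** From Sample size estimates: 54 per arm, effect size d = 0.60, 80% power, independent t test. The text reads "test with a significance level of 0.025" followed by a percent sign. The figure of 54 reproduces only if alpha is the proportion 0.025, two-sided; taken literally as 0.025%, about 113 per arm would be needed. Alpha = 0.025 is used below. The correlation r between pre- and post-program knowledge is not in the article, so r = 0.1 to 0.7 is an assumption.

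**Step 1: reproduce the plan.** The noncentrality is d × √(n/2) = 0.60 × √27 = 3.118. With 106 degrees of freedom the critical value is 2.274, and power is 79.9%. Solving for 80% gives 54.08 per arm. The sample size therefore takes no credit for baseline.

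**Step 2: fixed adjustment for baseline knowledge.** The residual SD becomes √(1 − r²), so the noncentrality is 3.118/√(1 − r²), with 105 degrees of freedom. The equivalent unadjusted sample size is 54/(1 − r²) per arm.

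| r (assumed) | 1 − r² | Noncentrality | Power | Equivalent n per arm |
|---|---|---|---|---|
| 0 (t test) | 1.00 | 3.118 | 79.9% | 54 |
| 0.1 | 0.99 | 3.133 | 80.4% | 55 |
| 0.2 | 0.96 | 3.182 | 81.7% | 56 |
| 0.3 | 0.91 | 3.268 | 83.8% | 59 |
| 0.5 | 0.75 | 3.600 | 90.6% | 72 |
| 0.7 | 0.51 | 4.366 | 98.1% | 106 |

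The effect detectable with 80% power falls from 0.60 to about 0.57, 0.52 and 0.43 at r = 0.3, 0.5 and 0.7.

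**Step 3: the imbalance-triggered rule.** The article gives no criterion, so imbalance is assumed to mean p < 0.05 for the baseline difference in knowledge. Simulation used 40,000 trials per setting, 54 per arm and normal scores. The trigger fires in about 5% of trials.

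| r (assumed) | Power, always adjust | Power, adjust only if imbalanced | Type I error, adjust only if imbalanced | Type I error, more favourable of the two reported |
|---|---|---|---|---|
| 0.3 | 83.6% | 80.4% | 2.3% | 3.2% |
| 0.5 | 90.1% | 81.2% | 2.1% | 3.9% |
| 0.7 | 98.0% | 81.6% | 1.5% | 4.1% |

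Nominal type I error is 2.5%. Followed strictly, the rule is slightly conservative and recovers little of the available power. Type I error rises only if an analyst may choose between the two results after seeing both.

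**Step 4: the two sentences on adjustment.** The first paragraph makes the primary analyses the object of adjustment. The second names the t test as primary and files adjustment under secondary analyses. They agree only if the first is read as a loose announcement of the second.

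**The case against.** The best defence is that the plan works as it stands. The t test is valid under randomisation, the trial is sized on that same test, and 54 per arm delivers the stated power. Over repeated randomisations the unadjusted estimate is unbiased, and its standard error already allows for chance imbalance. All of this stands: the loss is forgone precision, not underpowering.

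Four stronger readings are tempting, and the article does not support them:

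- **That chance imbalance picks the primary model.** This follows only from the first paragraph of Statistical analysis. The second fixes the t test as primary. The fair criticism is that the two conflict.
- **That baseline knowledge goes unused.** It is among the variables compared and available for adjustment, and it enters the paired tests and possibly the repeated-measures analysis. It is missing only from the main between-arm comparison.
- **That the gain is known to be large.** It depends on a correlation the article does not give. The background reports that 89% of community pharmacists had no earlier training in cessation counseling, and the program runs to about 32 contact hours, so a weak pre-post correlation in the trained arm is plausible. At r = 0.1 or 0.2 the gain is under 2 percentage points.
- **That the same gain applies to the OSCE.** The OSCE is taken only after the program, so it has no pre-test score, and nothing in the article quantifies a benefit there.

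A reader might also infer that the pre-test takes place after pharmacists learn their allocation. The text does not order the pre-test relative to that disclosure, and the flow chart and SPIRIT diagram are not available here, so the point is not made.

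The defence does not remove the rule itself. It is printed in the article, so it cannot be treated as detail left to an analysis plan.

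**Conclusion.** The point holds as a matter of efficiency and clarity. It does not threaten validity. For knowledge, the plan forgoes between almost nothing (r = 0.1) and about 18 percentage points of power (r = 0.7: 98.1% − 79.9%), with about 11 points at r = 0.5 (90.6% − 79.9%). These figures rest on the assumed correlations, a linear relation between the scores, and two-sided alpha of 0.025.

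The imbalance-triggered rule is a poor way to choose covariates under either reading of the text. The conflict over its role should be resolved before outcome data are seen. If either result could be called primary afterwards, the simulated type I error of about 3% to 4% against 2.5% shows the exposure. It arises only from that choice, which the article does not say will be made. The change is worth making because it costs almost nothing.

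**What to change.** - Make the primary knowledge analysis a linear regression of post-program score on arm, with baseline knowledge as a prespecified covariate whatever imbalance is seen.
- Delete the rule that admits covariates on observed imbalance. Baseline characteristics can still be described by arm.
- Keep the unadjusted t test on post-scores as a supportive analysis.
- Reconcile the two sentences in Statistical analysis so that one result is clearly primary.
- For the OSCE, baseline knowledge may be prespecified as a prognostic covariate, with no claim of a particular gain. If it is not, the t test should be stated as the single primary analysis for that outcome.

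**Cost:** a change of wording. The pre-program scores are already collected and linked, and linear regression is already planned. The sample size can stay at 54 evaluable per arm, with any gain taken as extra power. The Trial status section places recruitment and delivery still ahead, so on that timetable the change precedes any outcome data.

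### The only between-arm test named for attitudes and self-efficacy is a chi-squared test that leaves out the linked baseline responses, and the form of the simulated-client outcome is left open

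*Protocol article*

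**What the plan says.** Under Outcome measures, attitudes and self-efficacy after the program, measured by a survey instrument, are secondary outcomes, and so is simulated-client performance. The section on pre- and post-program assessment gives the survey to both arms before and after the program, with codes that link each participant's two responses.

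Under Statistical analysis, the knowledge and OSCE scores are compared by t test, with linear regression as an adjusted analysis. Attitude and self-efficacy appear only as examples in the next rule: "For outcomes that are dichotomous or that will be dichotomized, such as the percentage of pharmacists with a specific attitude or self-perceived efficacy". That rule gives chi-squared between arms and McNemar within each arm. A repeated-measures analysis is mentioned for outcomes generally, but only as an option.

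For the practice-setting outcome the section says: "Performance on the simulated patient will be compared in a similar manner as the outcomes above depending on whether it is dichotomized or not". The section on the simulated client describes assessment forms made up of yes/no items covering history-taking, assessment, treatment plan and counselling. It defines no summary score.

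Under Sample size estimates, "the study will be able to detect a difference of at least 27.5% between the two study groups for any dichotomous outcome", by chi-squared test at 80% power and 5%.

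**The concern.** The secondary objectives rest on these three outcomes. If a survey scale is reduced to the percentage of pharmacists on one side of a cut, much of the information in the score is lost, and the trial is weaker on these objectives than its size allows.

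The between-arm chi-squared test also ignores what each pharmacist answered at baseline. Those data are collected and linked, and they are usually the strongest predictor of the post-program answer. McNemar does use them, but within one arm, so it does not estimate the randomised comparison.

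For the simulated client, the plan writes in two forms of outcome and does not choose between them. That choice decides which test is run on the only outcome measured in practice.

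**Working it through.** **Inputs from the protocol article (Sample size estimates).** 54 evaluable pharmacists per group; chi-squared test, 80% power, 5% (taken as two-sided); detectable difference 27.5 percentage points; effect size 0.60 for the numeric primary outcomes. No control proportion is given.

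**Assumptions, not in the article.** The survey gives a roughly normal score with equal SD in both arms. The effect size of 0.60 is borrowed from the primary outcomes for illustration.

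**1. The plan's own figure.** n = [1.96·√(2p̄(1−p̄)) + 0.8416·√(p1(1−p1) + p2(1−p2))]² / (p1−p2)².
- Worst case, centred on 50% (36.25% v 63.75%): n = 50.7, so 51 per group. Power with 54 is 82%.
- 50% v 77.5%: n = 46.8 without continuity correction and 53.8 with it, so 54.

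The 27.5 points is therefore sound for an uncorrected test, and matches 54 exactly for one corrected case.

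**2. The same difference on the score scale.** For a normal score cut centrally, 36.25% v 63.75% is a shift of 2·Φ⁻¹(0.6375) = 0.70 SD. A t test with 54 per group has 95% power for that shift. The t test reaches 80% power at 0.54 SD.

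**3. Power for a true 0.60 SD difference, 54 per group, two-sided 5%.**
- Score, t test: non-centrality 0.60·√(54/2) = 3.12, 106 df, critical value 1.98; power 87%.
- Cut score: if a proportion p1 of controls lies above the cut, the intervention proportion is p2 = Φ(Φ⁻¹(p1) + 0.60). Power = Φ{[(p2−p1)√54 − 1.96√(2p̄(1−p̄))] / √(p1(1−p1) + p2(1−p2))}.

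| Controls above cut | Intervention above cut | Power |
|---|---|---|
| 20% | 40.5% | 64% |
| 30% | 53.0% | 68% |
| 38.2% (central) | 61.8% | 69% |
| 50% | 72.6% | 68% |
| 80% | 92.5% | 47% |

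Worked central case: (1.733 − 1.386)/0.687 = 0.505, and Φ(0.505) = 0.69. Worked 80% case: (0.921 − 0.954)/0.479 = −0.070, and Φ(−0.070) = 0.47.

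**4. Use of the baseline score.** With a pre-post correlation r, adjustment acts approximately as if the effect were 0.60/√(1−r²). The article gives no r. For r = 0.3, 0.5 and 0.7, power on the score is about 90%, 95% and 99%.

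**The case against.** The sentence on dichotomised outcomes is conditional. It assigns a test to binary outcomes and gives attitude and self-efficacy as examples. A reader might infer that the plan commits to cutting the scale scores. The text does not say so, and a percentage with a particular attitude could refer to a single survey item.

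A reader might also infer that a third of the information is certainly lost. That figure (36%) holds for a normal score cut at its median. The article states neither the scale nor the scoring, and an item answered yes/no loses nothing. The simulated-client items are of that kind, and the branch of the plan that does not dichotomise already allows a numeric score.

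A third inference would be that cuts will be picked after the data are seen. Nothing in the article says when cuts are set. Cut-points and item lists may well stand in a full protocol or analysis plan that is not shown, so their absence here is not held against the plan.

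The 47% figure is one end of a range, and no figure in the article suggests that 80% of controls start above a cut. The optional repeated-measures analysis could also bring in the baseline.

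All of this stands, and it narrows the point. It does not remove it: chi-squared is still the only definite between-arm test tied to these two outcomes, it leaves out linked baseline data, the repeated-measures analysis is optional, and the form of the simulated-client outcome is expressly undecided.

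**Conclusion.** The point holds in a limited form. The article names only a chi-squared comparison between arms for attitudes and self-efficacy, does not use the linked baseline in it, and leaves the simulated-client outcome in two possible forms.

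If the survey gives a roughly normal multi-item score and the true difference is 0.60 SD, keeping the score raises power from at most about 69% to 87%, before any gain from baseline adjustment. Where controls above the cut range from 20% to 80%, the power of the cut version runs from 47% to 69%. If the outcomes are single yes/no items, there is no loss from cutting, and only the unused baseline remains.

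The primary comparisons of knowledge and OSCE scores are numeric and not affected. This is a worthwhile improvement to the secondary analyses, not a flaw that threatens the trial's main result.

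**What to change.** In Statistical analysis:
- State that attitudes and self-efficacy are each compared between arms by linear regression of the post-program scale score on arm and the baseline score.
- State that simulated-client performance is analysed as the percentage of checklist items achieved, compared by the t test already named for numeric outcomes. This outcome has no baseline measurement.
- Report item-level or dichotomised percentages by arm descriptively.

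This changes wording only and needs no extra participants, visits or instruments. The small downside is that a difference on a scale is less intuitive than a percentage, which can still be tabulated beside it.
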